## Abstract

**Background:**

Depression in later life is a common mental disorder with a prevalence rate of between 3% and 35% for minor depression and approximately 2% for Major Depressive Disorder (MDD). The most common treatment modalities for MDD are antidepressant medication and psychological interventions. Recently, Behavioral Activation (BA) has gained renewed attention as an effective treatment modality in MDD. Although BA is considered an easy accessible intervention for both patients and health care workers (such as nurses), there is no research on the effectiveness of the intervention in inpatient depressed elderly.

The aim of study, described in the present proposal, is to examine the effects of BA when executed by nurses in an inpatient population of elderly persons with MDD.

**Methods/design:**

The study is designed as a multi-center cluster randomized controlled trial. BA, described as The Systematic Activation Method (SAM) will be compared with Treatment as Usual (TAU). We aim to include ten mental health care units in the Netherlands that will each participate as a control unit or an experimental unit. The patients will meet the following criteria: (1) a primary diagnosis of Major Depressive Disorder (MDD) according to the DSM-IV criteria; (2) 60 years or older; (3) able to read and write in Dutch; (4) have consented to participate via the informed consent procedure. Based on an effect size d = 0.7, we intend to include 51 participants per condition (n = 102). The SAM will be implemented within the experimental units as an adjunctive therapy to Treatment As Usual (TAU). All patients will be assessed at baseline, after eight weeks, and after six months. The primary outcome will be the level of depression measured by means of the Beck Depression Inventory (Dutch version). Other assessments will be activity level, mastery, costs, anxiety and quality of life.

**Discussion:**

To our knowledge this is the first study to test the effect of Behavioral Activation as a nursing intervention in an inpatient elderly population. This research has been approved by the medical research ethics committee for health-care settings in the Netherlands (No. NL26878.029.09) and is listed in the Dutch Trial Register (NTR No.1809).

## Background

Depression in later life is a common mental disorder. Prevalence rates for depressive symptoms range between 3% and 35%, for minor depression approximately 10% [1], and for Major Depressive Disorder (MDD) 2% [2]. The prognosis of MDD in later life is poor: in three quarters of cases, the disorder becomes chronic [3]. MDD has serious consequences for everyday life (e.g. withdrawal from social activities, neglect of one’s self-care), with a risk of increased health care consumption [4,5]. MDD has one of the largest disease burdens, comparable with other chronic diseases such as diabetes or COPD. About one third of patients with MDD will be referred to a mental health care facility (ambulatory or residential) [5]. The elderly are particularly at risk of developing persistent MDD because of their vulnerability to physical illnesses, which may contribute to the onset and persistence of MDD [6].

The most common treatment modalities for MDD are antidepressant medication and psychological interventions (or a combination thereof) [7]. Antidepressants seem to be efficacious in treating late-life depression, although the treatment outcomes may be less positive for the subpopulation of older elderly [8]. There are several psychotherapeutic options in depression treatment. Among adults in general, these different options are comparable in their effectiveness [9]. Recently, Behavioral Activation (BA) has gained renewed attention as an effective treatment modality in MDD. In BA, patients learn techniques to monitor their mood and daily activities and to gain insights into the connection between the two. The patients then learn how to develop a plan that increases the number of pleasant activities and positive interactions with their environment. A meta-analysis has demonstrated large effect sizes for BA interventions (d = 0.89) when compared to a waiting list condition [10]. Furthermore, direct comparisons between Cognitive Therapy (CT) and BA have demonstrated that the effectiveness of the two interventions is comparable [11,12]. Since BA seems to be more accessible for many patients than CT, BA might be a preferred treatment option. Another meta-analysis shows that, in general, psychotherapy seems to be as effective for older individuals as for younger adults [9]. However, this meta-analysis did not include studies focusing on severely depressed or hospitalized patients. In general, psychological treatments have been found to be less effective in outpatients with chronic depression [13], and possibly severe depression [14], although the evidence is not conclusive [15].

Inpatient treatment remains an important treatment option for patients who cannot safely stay in their own environment [16]. Many of these patients suffer from severe and chronic forms of depression, and effective treatment options are needed to improve their recovery and reduce their suffering. The number of studies on psychological treatment for inpatients is limited. Recently, we summarized those studies in a meta-analysis and demonstrated small but robust effects [17]. However, there was a considerable variation in treatment setting, content of treatment, number of sessions, and inclusion and exclusion criteria applied. Furthermore, the quality of most of the studies was not optimal.

To our knowledge, there is only one study in which BA is tested in an inpatient population [18]. In this study, a total of 25 inpatient depressed adults were allocated either to BA (N = 10) or to Supportive Psychotherapy (SP) (N = 15). Despite the small sample, the study demonstrated the effectiveness of BA, with an effect size of 0.73. It is noteworthy that in this study, BA was executed by clinicians who had Master’s degrees, although BA is supposed to be an intervention which requires no complex skills.

The aim of study described in the present proposal is to examine the effects of BA when executed by nurses (RNs) in an inpatient population of elderly people with MDD. In this study, BA takes the form of a brief behavioral course of treatment lasting seven weeks, known as the Systematic Activation Method (SAM).

## Methods/design

### Study design

The study is designed as a multi-center cluster randomized controlled trial with the participation of ten mental health-care facilities in the Netherlands. The Systematic Activation Method (SAM) will be compared with Treatment As Usual (TAU) for inpatient depressed elderly. In Figure 1 the study design is summerized.

**Figure 1 F1:**
[figure not shown]
Flowchart.

The study has been approved by the medical research ethics committee for health-care settings in the Netherlands (No. NL26878.029.09) and is listed in the Dutch Trial Register (NTR No. 1809). 

### The units and randomization

The study will include ten mental health care units, which will be randomized to the experimental (SAM) or control (TAU) conditions. The following inclusion criteria will be used to select the units: (1) the units must specialize in the treatment of elderly patients with psychiatric disorders; (2) there must be at least three registered nurses (RNs) available who are able and willing to execute the intervention. Units that specialize in a specific disorder or treatment method (e.g. Electro Convulsion Therapy) will be excluded from the study.

Within each mental health institute, the aim is to find two units which are comparable. Matching of units is based on two criteria which will be applied in the following order: (1) level of restraint – both units should either be open or closed; (2) the presence of other treatments containing elements of the SAM, i.e. occupational therapy (because it focuses on activation), psychological treatment (because it focuses on influencing cognition).

For matching purposes, staff members at the participating units will be asked to fill in a self-developed evaluation form providing information on the specific features of the unit. This form includes a number of general questions concerning characteristics of the patient group, followed by more specific questions about the treatment program and level of restraint.

After matching the units into pairs, one unit will be allocated to the experimental condition and the other to the control condition. Allocation will be performed by an independent researcher ([name]) who will not maintain contact with the participating units. A random allocation generator will be used.

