### Inclusion and exclusion criteria

The following patient inclusion criteria will be applied: (1) a primary diagnosis of Major Depressive Disorder (MDD) according to the DSM-IV criteria [19]. Patients with multiple diagnoses (e.g. comorbid personality disorder) are eligible as long as the primary diagnosis is MDD; (2) 60 years or older; (3) able to read and write in Dutch; (4) the patient must have consented to participation via the informed consent procedure.

Patients with severe cognitive problems (see below) will be excluded from this study because the intervention requires cognitive skills such as planning and evaluating activities and the structured monitoring of mood state.

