### Recruitment of the study sample

The participating units will keep a list of all newly admitted patients and their primary diagnosis. All patients older than 60 with a primary diagnosis of MDD will be approached by a staff member and informed about the study. Once verbal consent is obtained and there are no cognitive problems according to the Minimal Mental State Examination (MMSE score ≥ 23) [20], the patients will be approached by one of the researchers. Confirmation of the psychiatric diagnosis will be executed by means of a diagnostic interview using the MINI Plus, a standardized instrument to assess psychiatric disorders according to the DSM-IV criteria [21]. Patients who satisfy the inclusion criteria will then be included in the study. Due to the nature of the intervention, it will not be possible to perform the study as either a single-blind or double-blind trial.

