The SAM requires the patient’s active involvement. This is often difficult due to the nature of MDD. The nurses participating in this study will therefore be given a brief training course of two four-hour sessions on guiding patients in executing the SAM. Training consists of two components. First, the nurses will be taught the structure and process of the SAM. Second, they will be trained in using motivational techniques. Many patients with MDD have difficulty engaging in structured activities, this being one of the essential components of the SAM. The use of motivational techniques is therefore vital for the effective execution of the SAM.

During the study, the participating nurses will receive training on the job, with the researcher visiting the units for in biweekly supervision meetings. In addition, the researcher will maintain telephone and e-mail contact. During the supervision meetings, the nurses will be invited to reflect on their experiences during execution of the SAM intervention and – in the event of problematic implementation – adjustments and alternative strategies can be discussed. The biweekly meetings will therefore be used to establish treatment integrity, along with a random audit of the course books and a written evaluation by the patients in order to register the received components of the SAM intervention.

The participating patients will receive the SAM as an individual adjunctive therapy combined with their existing primary treatment.

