### Control group

The control group will receive Treatment As Usual (TAU). The most common treatment for patients with MDD is a combination of medication, occupational therapy and a form of psychological treatment such as Cognitive Behavioral Therapy (CBT) or Problem Solving Treatment (PST). Nursing care focuses on assisting patients in their self-care activities, and encouraging them to participate in the unit’s daily activity program. Nurses also discuss the patient’s overall progress on a regular basis (weekly or biweekly). TAU is recorded at unit level. Before participating in the study, the units describe their treatment program for MDD using a structured form developed by the authors. This form is based on the NICE standard for MDD [7] and the Dutch guideline for MDD [29].

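### The plan leaves routes by which SAM could reach control patients, and no record it states would show that it had

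*Protocol article*

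**What the plan says.** **Allocation.** The units and randomization seeks matched pairs: "Within each mental health institute, the aim is to find two units which are comparable". Within a pair, "After matching the units into pairs, one unit will be allocated to the experimental condition and the other to the control condition". The first matching criterion is "level of restraint – both units should either be open or closed". The second is the presence of other treatments that share elements with SAM.

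**Eligibility.** Inclusion and exclusion criteria requires a primary diagnosis of MDD, age 60 or over, Dutch literacy and consent. The one stated exclusion is cognitive: "Patients with severe cognitive problems (see below) will be excluded from this study because the intervention requires cognitive skills". Recruitment of the study sample adds that "The participating units will keep a list of all newly admitted patients and their primary diagnosis", and that patients who meet the criteria are then included. Neither section mentions earlier SAM or earlier enrolment.

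**SAM outside the randomised comparison.** Ethical considerations makes two statements. Patients who are excluded from the study may still be given SAM. SAM is introduced on the control units once inclusion is complete.

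**Recording of exposure.** Intervention lists supervision meetings, a course-book audit and "a written evaluation by the patients in order to register the received components of the SAM intervention". For the other arm, Control group says: "TAU is recorded at unit level. Before participating in the study, the units describe their treatment program for MDD using a structured form".

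**Follow-up.** Assessment and Table 1 place T1 at 8 weeks and T2 at 6 months after baseline.

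**The concern.** The comparison is SAM added to TAU against TAU alone, so it depends on control patients not receiving SAM up to their last assessment. As written, a control patient could have had SAM before enrolment, or could meet it on the control unit before T1 or T2. No stated instrument would identify that patient. If SAM is effective, such exposure shrinks the observed difference. A null result could then mean either that SAM does not work or that the control arm was partly treated, and the data would not separate the two. A patient enrolled twice would also contribute two non-independent records, possibly one in each arm.

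The authors treat overlap between arms as important, since they match units on treatments that resemble SAM. But the attention stops at allocation. The Discussion names selection bias, information bias and variable delivery as difficulties, and does not mention contamination.

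**Working it through.** **Step 1: is prior exposure excluded?** The four inclusion criteria and the single cognitive exclusion were read together with the recruitment steps. A patient who had SAM outside the study, or was enrolled during an earlier admission, satisfies them on a later admission. So prior exposure is not excluded.

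**Step 2: does the roll-out start after control follow-up ends?** Ethical considerations ties it to the end of inclusion. Recruitment of the study sample uses inclusion to mean enrolment. Let the last inclusion occur at time 0.
- A control patient included less than 8 weeks before time 0 still has T1 and T2 to come.
- A control patient included less than 6 months before time 0 still has T2 to come.
- SAM is a seven-week course and T1 is at 8 weeks. A patient enrolled at the very end and still on the unit could, if roll-out were immediate, complete the course before T1 (7 < 8).

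The documents do not give length of stay or the actual roll-out date. This shows that overlap is possible, not that it will occur.

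**Step 3: would exposure of a control patient be seen?**

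| Source | Level and timing | Shows SAM received by a control patient? |
|---|---|---|
| Course-book audit, patient evaluation, supervision | Described for SAM delivery | No |
| TAU form | Unit, before participation | No |
| Baseline treatment history | Patient, T0 | Perhaps some earlier exposure; SAM is not named |
| TiC-P and Activity Log | Patient, T0 and T2 | SAM is not named |

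Exposure during follow-up is therefore not captured by any stated record.

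**Step 4: reproduce the plan's sample size.** Inputs from Sample size: d = 0.7, α = 0.05, power 0.80, 25% for dropout, 25% for clustering. A two-sided two-sample t-test (noncentral t) needs 33.02 per arm, hence 34, as stated. Adding the two allowances gives 34 × (1 + 0.25 + 0.25) = 51 per arm and 102 in total, as stated. No term allows for dilution.

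**Step 5: illustrate the sensitivity.** Let c be the share of the effect lost, so that d_eff = 0.7 × (1 − c). The values of c are assumptions. Power is for 34 evaluable patients per arm, with no further loss from clustering and an unchanged standard deviation. The last two columns show what 80% power would need; total N uses the plan's own factor of 1.5, rounded up per arm.

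| c | d_eff | Power at 34 per arm | n per arm for 80% | Total N |
|---|---|---|---|---|
| 0 | 0.70 | 0.81 | 34 | 102 |
| 10% | 0.63 | 0.73 | 41 | 124 |
| 20% | 0.56 | 0.62 | 52 | 156 |
| 30% | 0.49 | 0.51 | 67 | 202 |

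c equals the share of controls exposed only if each exposed control receives the full effect. Otherwise it is smaller: 20% exposed at half the effect gives c = 0.20 × 0.5 = 10%.

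**The case against.** The strongest defence is that the design already contains the standard protection. Units, not patients, are randomised. Pairing within an institute makes the arms comparable. SAM is a structured individual course with a course book, homework, nurse training and supervision, so casual contact is unlikely to deliver its full effect. A condensed article may also leave operational rules to the full protocol. Much of this stands. It lowers the likely size of the problem and rules out several stronger readings that a reader might infer:

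- **The pairing is itself an error.** It is not. It serves comparability, is stated as an aim, and need not change.
- **SAM-trained nurses work on the paired control unit.** No section says so. The plan requires at least three registered nurses in each unit and describes supervision as visits to the units. A demand about rosters would rest on silence alone.
- **Readmission to the control unit is expected.** Background describes a chronic course, and Assessment records former treatments and admissions. Neither establishes that a patient who has had SAM returns to the paired control unit during recruitment. It is possible, no more.
- **The design contradicts itself on the number of sites.** Study design speaks of a trial "with the participation of ten mental health-care facilities in the Netherlands", while the Abstract and The units and randomization speak of ten units. This reads as loose wording.
- **Power will fall to 0.73 or 0.62.** The documents give no exposure rate, so these figures are illustrative.

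The defence does not answer what the article fixes explicitly: an eligibility list that admits prior exposure, a roll-out tied to inclusion instead of follow-up, SAM for patients outside the study, and exposure records that do not cover the control arm. The general baseline history helps somewhat with earlier treatment but not with exposure during follow-up. Intention-to-treat analysis keeps patients in their allocated arm but does not reveal or undo exposure.

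**Conclusion.** The concern holds in a limited form. The text leaves identifiable routes for SAM to reach control patients, and no stated record would detect it during follow-up. Given an effective SAM, the expected direction of bias is toward no effect. Its size cannot be derived from the documents and may be small. The planned sample has little reserve: it starts at 0.81 power, so even a modest loss of effect takes it below the 0.80 target.

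This rests on three readings: that inclusion means enrolment in the roll-out sentence, as it does in the recruitment section; that the stated eligibility list is complete; and that some late control patients could still be on, or return to, the unit when SAM is introduced there. It does not rest on shared staff or on an expected rate of readmission. The change is worth making because it is cheap and protects the interpretation of a null result.

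**What to change.** 1. **Inclusion and exclusion criteria:** add that patients previously enrolled in the study, or previously given SAM in or outside it, are not eligible.
2. **Ethical considerations:** reconcile the roll-out statement with the follow-up schedule, so that SAM is not introduced on control units before the last control patient's T2.
3. **Assessment:** for every patient in both arms, record at T1 and T2 any SAM received and any transfer between units. Use neutral wording, because a detailed list of SAM components could itself convey them to control patients. Report exposure by arm, with a sensitivity analysis that takes it into account.

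As a minor wording point, align facilities with units in Study design.

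**Cost:** a few readmitted patients lost to recruitment, a later roll-out to control units, and a few extra questionnaire items. The randomisation, the pairing and the primary outcome stay as they are.

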### Inclusion and exclusion criteria

The following patient inclusion criteria will be applied: (1) a primary diagnosis of Major Depressive Disorder (MDD) according to the DSM-IV criteria [19]. Patients with multiple diagnoses (e.g. comorbid personality disorder) are eligible as long as the primary diagnosis is MDD; (2) 60 years or older; (3) able to read and write in Dutch; (4) the patient must have consented to participation via the informed consent procedure.

Patients with severe cognitive problems (see below) will be excluded from this study because the intervention requires cognitive skills such as planning and evaluating activities and the structured monitoring of mood state.

### Recruitment of the study sample

The participating units will keep a list of all newly admitted patients and their primary diagnosis. All patients older than 60 with a primary diagnosis of MDD will be approached by a staff member and informed about the study. Once verbal consent is obtained and there are no cognitive problems according to the Minimal Mental State Examination (MMSE score ≥ 23) [20], the patients will be approached by one of the researchers. Confirmation of the psychiatric diagnosis will be executed by means of a diagnostic interview using the MINI Plus, a standardized instrument to assess psychiatric disorders according to the DSM-IV criteria [21]. Patients who satisfy the inclusion criteria will then be included in the study. Due to the nature of the intervention, it will not be possible to perform the study as either a single-blind or double-blind trial.

### Intervention

We developed the Systematic Activation Method (SAM) as a brief behavioral nursing intervention which focuses on increasing a positive mood change by increasing the number of positive activities. The SAM is based on Behavioral Activation (BA), developed by Lewinsohn and colleagues [22-27] and Hopko et al. [18]. The underlying assumption is that positive reinforcement of a low response rate acts as an eliciting stimulus for depressive behaviors and serves as a sufficient explanation for inactivity in a depressed individual [27]. The SAM is presented as a brief seven-week course. In order to make the SAM accessible for the elderly inpatient population, we have made some adjustments to the existing BA protocols. First, the goals of each session are described in the course book. This differs from the existing protocols, in which the first session is used for mutual goal setting. It is difficult to describe the overall goals of treatment for inpatient elderly with MDD; that is why the goals have been described at the beginning of each session. Second, the course is presented as a nursing intervention instead of a psychological intervention in order to increase its accessibility. Third, we simplified the activity logs to avoid overloading the patients. Fourth, the duration of the intervention has been shortened to seven weeks, in contrast to the existing treatment protocols, which last between eight and 15 weeks.

The SAM consists of six sequential steps: 1) monitoring the patient’s mood; 2) having the patient execute pleasant activities, randomly selected from an existing list of 49 activities [25]; 3) having the patient develop a positive activity plan; 4) having the patient explore how to use external resources; 5) setting up an activity experiment; 6) evaluation and consolidation. There is a one-week time interval for each step except the third step (developing a positive activity plan), for which two one-week intervals are required. If necessary, the time interval between the sessions can be reduced or extend. Each session is highly structured and starts with a review of the patient’s homework. After that, the nurse and patient discuss the central theme of the session and the patient is given his or her homework assignments for the coming week. The SAM is described in more detail by Clignet, Van Meijel, Van Straten, Lampe and Cuijpers [28].

The SAM requires the patient’s active involvement. This is often difficult due to the nature of MDD. The nurses participating in this study will therefore be given a brief training course of two four-hour sessions on guiding patients in executing the SAM. Training consists of two components. First, the nurses will be taught the structure and process of the SAM. Second, they will be trained in using motivational techniques. Many patients with MDD have difficulty engaging in structured activities, this being one of the essential components of the SAM. The use of motivational techniques is therefore vital for the effective execution of the SAM.

During the study, the participating nurses will receive training on the job, with the researcher visiting the units for in biweekly supervision meetings. In addition, the researcher will maintain telephone and e-mail contact. During the supervision meetings, the nurses will be invited to reflect on their experiences during execution of the SAM intervention and – in the event of problematic implementation – adjustments and alternative strategies can be discussed. The biweekly meetings will therefore be used to establish treatment integrity, along with a random audit of the course books and a written evaluation by the patients in order to register the received components of the SAM intervention.

The participating patients will receive the SAM as an individual adjunctive therapy combined with their existing primary treatment.

